## Methods/design

### Aim 1: Develop an integrated intervention consisting of moral case deliberation (MCD)

#### Dialogue method

To structure a MCD session, a variety of dialogue methods can be chosen [26]. Within this project the ‘Dilemma Method’ will form the basis of the intervention. The method is considered suitable for the work setting, as this method offers the most tangible and down-to-earth approach of the situation, and it is suitable for both life-or-death decisions and everyday issues. The MCD sessions will be guided by trained facilitators ([name], [name]). The facilitator functions as a non-directive facilitator as opposed to an expert and concentrates on the quality of the deliberation process by guarding the quality of the dialogue [23, 26]. In the MCD sessions, there are six to twelve participants.

#### Continuous adaptations intervention

Responsive Evaluation allows for continuous adaptation of the intervention to the (changing) context and needs for the target population. There are some adaptations that can be expected upfront. Firstly, the level of the language used in the dialogue sessions and other forms of communication will be adapted to match the literacy level of the participants. Abstract use of (ethical) concepts will be avoided and all forms of communication will be adjusted to B1 literacy level. Secondly, to match the work context, the timing of the MCD sessions have to be adapted to be both feasible and relevant for the organisation. The duration of the MCD sessions will therefore be reduced from the duration of 1,5 h (which is common in settings in which MCD is often performed, such as health care, detention, army), to 1 h. Further adaptations will be carried out throughout the evaluation period.

#### Recruitment

The aim is to include a maximum variety of stakeholders in the dialogues in order to capture a broad range of experiences and perspectives. Stakeholders will be contacted by means of a contact person in the participating organisations or directly and selected based on their willingness to participate.

### Aim 2: Evaluate the implementation of and changes due to MCD

#### Study design

A Responsive Evaluation design will be used to evaluate the implementation and the eventual changes due to MCD. As described before, Responsive Evaluation is characterized by stakeholder involvement, yet the degree of involvement may range from collaborative evaluation, participatory evaluation and empowerment evaluation [27]. The evaluation in this project has the ‘lightest’ degree of participation, namely collaborative evaluation. In collaborative evaluation, stakeholders are consulted and involved in the evaluation, but the evaluator remains in mainly in charge of the decisions, thus power.

The implementation and impact of the intervention will be evaluated both at fixed moments as well as continuously. The fixed moments are at the beginning of the project (baseline) and a yearly evaluation. The minimum duration of the intervention is 1 year, with a maximum of 2 years. The baseline and yearly evaluation comprise mixed methods such as interviews, participatory observations and analyses of HRM-data. Continuous evaluation comprises participatory observations and short questionnaires. Figure 1 provides a schematic overview of the Responsive Evaluation. The overview includes the economic evaluation (aim 3).

**Fig. 1 Fig1:**
[figure not shown]
Schematic overview of the Responsive and Economic Evaluation (1 year minimum, 2 years maximum)

#### Study population

The study population consists of lower SEP employees within two Dutch organisations (maximum MBO 1 – comparable to middle school- or lower [6]). The intervention will be implemented in two organisations, namely a harbour service provider, and a sheltered workplace for employees with disabilities. Higher SEP employees are not excluded from the intervention: the intervention is based on the rationale that it should lead to changes in the context. Therefore, the entire all employees of the organisations should be allowed to participate. All employees may benefit from the intervention, however, as health problems are more prevalent for lower SEP employees, they are expected to benefit most from the intervention. Names of the organizations will not be made public, only in case of explicit written consent of each organisation.

#### Data collection

##### Baseline

At baseline, information about relevant changes as a result of the intervention according to the stakeholders, prerequisites for participation and for the adaptation of the MCD sessions to the specific work context, and information about the work setting will be gathered. The three aims will be discussed separately below:

#### Relevant changes as a result of the intervention

Relevant changes are those changes that are considered important from the perspectives of the various stakeholders. For the management and staff, a relevant change might be improved job satisfaction, mutual understanding or general well-being of employees. Some examples of relevant changes for line-managers and employees might be for example learn about how to deal with stressful situation at work, improved communication in the organisation or contribute to a culture in which a healthy lifestyle is promoted.

#### Prerequisites for participation and for adaptation of MCD to the work context

Prerequisites for participation are important, as it is not self-evident for employees to come to the table and talk about health. Also other stakeholders such as the management might have time related restrictions in their possibilities to participate in the dialogues. Prerequisites include suitable timing of the MCD sessions, duration and composition of the group. As described before, the lower SEP employees are the starting point for the question who would they like to be in dialogue with. This will be re-evaluated throughout the intervention period.

#### Insight into the work setting

Insight into the work context (type of work, the working conditions, terminology) of the organisation is necessary for better and correct interpretation of the data. To obtain the information for the baseline, the following methods will be used:

#### Interviews

Interviews will be held with approximately 6 stakeholders. The interviews will be audio recorded and transcribed verbatim.

#### Participatory observations

Job shadowing (i.e. participating in meetings and work routines) will be performed by the researchers, as a means to help interpret interview findings [28]. In addition, participatory observations are a means to build trust in the organisations. This trust is important to create a safe communication climate in the dialogues [24]. The quantity of participatory observations at baseline will depend on the possibilities and flexibility within the organisations. Field notes will be taken during or shortly after the observations. Researchers ([name] and [name]) will discuss their observations afterwards.

#### HRM-data analyses

HRM data will be used to analyse relevant changes that were formulated by stakeholders. These changes will be evaluated yearly. The type of data depends on the changes considered relevant by the various stakeholders, but could for example include indicators such as job satisfaction.

##### Change evaluation

The goal of the change evaluation is to gain insight in perceived changes, personal experiences, and attitudes towards the intervention according to the stakeholders [29]. The methods of that were used at baseline will partly be repeated, including interviews, participatory observations, and HRM-data. Additionally, transcripts of the MCD sessions will be used as input of the further process, subtract feedback, intermediate findings and relevant topics for subsequent MCD sessions.

#### Data analysis

##### Qualitative data

Qualitative data will be analysed through thematic content analysis [30]. For the baseline and MCD data, the data will be the starting point of the analysis instead of a theoretically-driven or predefined coding scheme (inductive approach). Within the inductive approach both semantic and latent strategies will be used. Semantic strategies (descriptive codes)**,** are used to code practical information about the work context and terminology. The latent strategy (codes that require interpretation) will be used to analyse underlying ideas, mechanisms and values.

For the annual evaluation, a deductive inductive approach will be applied. First, a deductive approach will be applied to analyse the data on the existence of changes. The division of levels of aims/outcomes of MCD will be used (case, individual, team and organisational) [31]. Subsequently, an inductive approach will be applied in order to analyse any underlying mechanisms, mechanisms and values in the data.

#### Enhancing quality

To enhance quality, reliability and validity of the qualitative data, several techniques will be taken into account [28]. First, interpretations of interviews will be presented to interviewees to verify correctness *(member check).* Also, multiple data sources (such as interviews and participatory observations) will be used and combined in analyses *(data triangulation).* Third, data will be coded by (at least) two researchers ([name], [name]) and discussed within the multidisciplinary research team *(investigator triangulation).* Fourth, the researchers (post-doc and PhD) will keep a diary to reflect on their role and influence in the research process *(reflexivity)*. Finally, researchers ([name] and [name]) will document decisions and developments, and the underlying reasons *(audit trail)*.

##### Quantitative data

Change indicators of HRM data are monitored over time, taking into account different organisational levels and subgroups of employees. Therefore, these quantitative data will be analysed according to principles of longitudinal multilevel regression analysis. Change will be determined from the perspective of all employees, but there will be a specific focus on the health related changes among lower SEP employees (subgroup analyses).

### Aim 3: Economic evaluation of the stakeholder dialogue intervention

The intervention will also be evaluated economically, through a Budget Impact Analysis (BIA) and a Social Return on Investment (SROI) analysis.

### Budget impact analysis (BIA)

A BIA is a means to analyse the financial changes after the adoption of a new intervention, by comparing costs before and afterwards the intervention [32]. Examples of costs that can be compared pre and post intervention are productivity related costs or absence and presenteeism related costs. Which costs will be chosen depends on what data is available in the organisation. A possible change in costs will be measured yearly compared to a baseline measure. The eventual change in costs will be compared to the investment made for the intervention. For this project the investment comprises the costs for the MCD sessions, such as costs for the time stakeholders spent on participating in the intervention, for training and implementation of facilitators, and for overhead.

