## Discussion

This paper describes the study protocol of the development and evaluation of moral case deliberation (MCD) as a worksite health promotion (WHP) intervention. MCD was chosen as a form of stakeholder dialogue because it pays attention to the multiplicity of values and interests in WHP and moral dilemmas at stake, employees’ lived experiences and power asymmetries in the work context. Responsive Evaluation was proposed as the type of evaluation of this study. This study will add to the current body of literature of WHP, as it provides a novel intervention as well as an original type of evaluation in the field of WHP.

The strength of this study is that Responsive Evaluation allows to respond to the dynamic and ambiguous context of the work setting. Organisations are constantly changing due to internal and external developments, which also changes the context in which WHP interventions are being performed. In order to maintain appropriateness of the intervention in a changed situation, Responsive Evaluation as well as the intervention offer the flexibility to adapt research goals and activities during the research process [24]. Ambiguity in the work setting is a result of power relations such as the dependency relationship between employer and employee. These power relations are also reflected in WHP, where the employer is in charge and the employee has little or no voice in WHP. The starting point of Responsive Evaluation is a bases of equality among various stakeholders [24, 34], as well as special attention to silenced voices such as employees in WHP, which makes this type of evaluation very suitable for the work setting.

To date, Responsive Evaluation is considered innovative in the field of WHP, where a Randomized Controlled Trial (RCT) is the gold standard. A RCT aims to evaluate causality by randomizing participants in an intervention and control group, and correcting for bias in the analysis [35]. One important difference between both types of evaluation is that Responsive Evaluation does not aim to evaluate causality. Instead, Responsive Evaluation aims to support the stakeholders in the setting under study to better understand their context themselves, which allows and supports them to make relevant practice improvements.

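### The budget impact analysis sets the whole cost change since one baseline measure against the MCD investment, with nothing to separate out background change

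*Protocol article*

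**What the plan says.** The section Budget impact analysis (BIA) defines the analysis as a contrast made "by comparing costs before and afterwards the intervention". It then fixes the reference point, "A possible change in costs will be measured yearly compared to a baseline measure", and the use of the result: "The eventual change in costs will be compared to the investment made for the intervention". The cost items depend on which data each organisation holds; the time at which the list is fixed is not given.

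Under Study design, "The fixed moments are at the beginning of the project (baseline) and a yearly evaluation", and "The minimum duration of the intervention is 1 year, with a maximum of 2 years". That leaves one or two yearly values after baseline. Under Study population, MCD goes to both participating organisations and is open to all their employees, so no unexposed group is planned.

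Three other places bear on how the result will be read:

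- Objectives: the third objective is to evaluate MCD's economic impact, with the BIA as the monetary part.
- Discussion: "Organisations are constantly changing due to internal and external developments".
- Data for SROI: the Social Return on Investment (SROI) analysis collects percentages for displacement, drop-off and attribution, to refine the value assigned to the outcomes. The BIA section has no such step.

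**The concern.** With one pre-intervention value and no unexposed unit, calendar time and MCD are the same variable. Anything that moves costs between baseline and follow-up becomes part of the change: a trend already under way, an unusual baseline year, a change in headcount, or wage and price rises. The BIA carries that total forward and nets it against the investment. The netting is informative about MCD only if the change can be attributed to MCD.

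The protocol itself says that its organisations keep changing for other reasons, and it plans to allow for such influences in one half of aim 3 (the SROI) but not in the other. At stake is whether the net figure can be read as the impact of MCD, which is how the objective words it. An organisation could be shown a saving or a loss that would have occurred anyway.

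**Working it through.** **No plan figure to reproduce.** The article states no cost level, cost variability, effect size or sample size. The structural point needs none of these; it follows from the stated contrast. The figures below only illustrate scale, and their variability and trend values are assumptions.

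**1. Chance variation with one baseline year.** Let yearly cost in an organisation vary around a constant mean with SD s (as % of the mean), with independent years and no MCD effect. The change from one baseline year to one later year has SD √2·s, and its 95% range is ±1.96·√2·s.

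| Assumed s | 95% range of change | Chance of an apparent saving above 5% |
|---|---|---|
| 2% | 1.96 × 1.414 × 2 = ±5.5% | 4% |
| 5% | 1.96 × 1.414 × 5 = ±13.9% | 24% |
| 10% | 1.96 × 1.414 × 10 = ±27.7% | 36% |

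A simulation with 200,000 replicates agrees. If neighbouring years correlate at 0.5, the SD of the change falls to s·√(2 × 0.5) = s, and the ranges are ±3.9%, ±9.8% and ±19.6%.

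**2. Background trend.** A trend of t per year passes wholly into the estimate. For an assumed t = 3%, that is 3% at one year and 2 × 3% = 6% at two years.

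**3. What earlier years buy.** This decides how the fix should be built. With three annual pre-intervention values and independent errors, the SD of the first post-start deviation is:

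- one baseline year: √2·s = 1.41s
- mean of three years: √(1 + 1/3)·s = 1.15s
- linear trend fitted to the three years: √(1 + 1/3 + 2)·s = 1.83s in year one, and √(1 + 1/3 + 4.5)·s = 2.42s in year two

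At s = 5%, the year-one 95% ranges are ±13.9%, ±11.3% and 1.96 × 1.83 × 5 = ±17.9%. With correlation 0.5, averaging gains nothing (±9.8% with one year, ±10.0% with three).

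The mean also has a cost when there is a trend. The centre of the three pre-intervention years lies two years before the first post-start year, so the bias there is 2t instead of t.

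Earlier years therefore do not mainly buy precision. They show how far costs move without MCD and whether a trend was already present. A trend-adjusted estimate from a short series removes that bias but is noisier, so it belongs in a sensitivity analysis.

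**The case against.** **No causal claim is intended.** The Discussion says that Responsive Evaluation is not meant to establish causality and contrasts it with a randomised trial. The BIA section speaks of a possible change and can be read as plain description. This has weight, but the disclaimer concerns Responsive Evaluation, the method of aim 2, and is not repeated for the BIA. Objective 3 is worded as impact, and setting a change against an investment invites that reading. If only description is meant, the wording still has to change.

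**A fuller document may give details.** It may, but the contrast criticised here is stated in the article. A fuller plan would have to alter it, not fill a gap.

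Some stronger readings are tempting and not supported:

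- **The HRM analysis has the same defect.** Under Study design, "The baseline and yearly evaluation comprise mixed methods such as interviews, participatory observations and analyses of HRM-data", which suggests a single baseline. But Quantitative data says only that "Change indicators of HRM data are monitored over time" and plans longitudinal multilevel regression without giving the number of time points. Routine records may reach further back, and the causality disclaimer does apply to aim 2.
- **Costs will be chosen after results are seen.** The text ties the choice to data availability and leaves its timing open. Late choice is possible, not planned.
- **The BIA is a headline result, or the HRM data are aim 2's only quantitative evidence.** The article ranks no outcomes, and it also lists short questionnaires.
- **Drift will exceed the cost of the sessions.** No cost figures are given, so any euro comparison would be invented.
- **Non-participating teams would be a safe control.** Participants are selected on willingness, access is open to all, and MCD is meant to change the shared context. Such teams would be self-selected and partly exposed, with bias possible in either direction.

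**Conclusion.** The concern holds for the BIA. As written, its net figure mixes any effect of MCD with background trend, yearly variation, headcount and price changes, and nothing in the BIA section separates them. That conclusion rests on the stated design alone. Its size is unknown: the ranges above (±5.5% to ±27.7% with independent years, ±3.9% to ±19.6% with correlation 0.5) depend wholly on the assumed SD of 2% to 10%. For the HRM analysis, a single baseline is only an inference from the evaluation schedule, so that analysis is not shown to be wrong. This calls for a correction to the BIA and its labelling, not for a redesign of the study.

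**What to change.** In Budget impact analysis (BIA), replace the single baseline comparison with the following:

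1. Fix the list of cost items for each organisation before any post-start data are seen.
2. Extract those items from routine records for several years before the first MCD session, monthly or quarterly where available.
3. Express them per FTE at constant prices.
4. Show post-start costs against the pre-intervention level and its year-to-year range. Where the history is long enough, add a result adjusted for the pre-intervention trend as a sensitivity analysis.
5. Apply to the BIA the attribution step already planned for the SROI. This remains a judgement and not a control, so show how the result changes with it.
6. Report the net budget impact with a range.

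If earlier records cannot be obtained, call the result a descriptive before-after change and not the impact of MCD, and align Objective 3 with that. The HRM analysis should use the same earlier records where they exist. Non-participating teams should not serve as the main control.

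The cost is a larger data extract and somewhat more analysis. Some indicators will have short histories, and the interval widens when a trend is fitted (1.83s against 1.41s in the three-year example).

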### Social return on investment (SROI)

The non-monetary economic evaluation will be performed through Social Return on Investment (SROI). SROI is a framework for measuring change in social, environmental and economic outcomes that are relevant to stakeholders and uses monetary values to represent them [33]. Data for the SROI will be gathered yearly by interviewing stakeholders that are relevant for the specific context of the participating organization. Stakeholders of SROI are defined as people or organisations that experience change, whether positive or negative, as a result of the activity being analysed [33].

#### Data for SROI

In order to perform a SROI, data needs to be collected on input, output, outcomes, indicators, financial proxies and contribution of the intervention [33]. Input refers to what investment the intervention entails for each stakeholder, such as time or money. Output refers to what is concretely delivered as part of the intervention, such as a certain amount of stakeholder dialogues. The outcomes are the changes perceived by stakeholders, as established in the responsive evaluation. General examples of outcomes given by the SROI Guide (2012) [33] are ‘reduced social isolation’, or an ‘increase in recycling’. Indicators are the concrete expression of the outcome, such as ‘frequency of social contact with friends’ and ‘amount of waste going to landfill’. Once the outcomes and indicators are mapped, financial proxies i.e. monetary values have to be given to the defined outcomes. There are several strategies to find these financial proxies (SROI guide). An example of a strategy is ‘Revealed Preference’, in which financial proxies are defined by inferring valuation from the prices of related market-traded goods. At last, data should be collected on the extent to which the intervention has contributed to the outcomes (attribution, drop-off and displacement). These factors are measured as percentages and are used to make a more accurate estimate of the total value of the outcomes.

